#### Provisions for post-trial care {30}

Participants are encouraged to seek evaluation and/or treatment from their usual sources of healthcare for any adverse health symptoms or problems that develop during the trial. If a participant recruited from UCSF is harmed because of study participation, the University of California will provide necessary medical treatment, with the costs of the treatment being billed to the participant or the participant’s insurer similar to other medical costs, or covered by the University of California depending on a number of factors. At Stanford University, if a participant develops medical complications from participating in this study, she will be assisted in obtaining appropriate medical treatment; in the event that the injury or illness is directly caused by study participation, reimbursement for all related costs of care first will be sought from the participant’s insurer, managed care plan, or other benefits program, and the participant will be responsible for any associated co-payments or deductibles as required by her insurance. The study institutions do not anticipate providing any other form of compensation for injury.

### Outcomes {12}

The primary outcome of change in composite cognitive function over 24 weeks of treatment is assessed using a standardized battery of neuropsychological tests selected for their sensitivity in evaluating relevant cognitive domains and feasibility of administration during either in-person or telehealth visits. Study coordinators undergo dedicated standardized training in administering these tests by a neuropsychology co-investigator, who also oversees the quality of these assessments. Specific tests include the following:The Rey Auditory Verbal Learning Test (AVLT) [39–41]The oral version of the Trail Making Test (OTMT) [42–45]The Digit Span Test from the Wechsler Adult Intelligence Scale [46]The Digit Symbol Substitution Test (DSST) [47, 48]

Baseline data on cognitive test performance in the full sample of randomized participants will provide the normative standard for cognitive test performance at both baseline and follow-up visits. For each cognitive test (or test component), the mean score from baseline administration of the test in the overall study population will be subtracted from each individual participant’s test score, and this difference will be divided by the standard deviation of test scores from the baseline trial population. After scores from individual cognitive tests are transformed to *Z* scores as a common metric using this approach, the average *Z* score from all available tests completed by each participant at each visit will be calculated to provide a composite *Z* score for the participant at that visit. The primary outcome will be described as the modeled mean change from baseline in this composite cognitive *Z* score at 4, 12, and 24 weeks, averaged over these time points.

Secondary domain-specific cognitive outcomes are defined by model-based mean changes from baseline in scores on each of the above individual cognitive tests (AVLT total learning, AVLT delayed free recall, OTMT part A, OTMT part B, Digit Span Test backward component, and DSST), also assessed over 24 weeks of treatment (averaged over 4, 12, and 24 weeks). Additional secondary cognitive outcomes are defined by modeled mean persistent difference in composite cognitive function score as well as scores on each of the above domain-specific cognitive tests at 12 weeks after the end of treatment (36 weeks after randomization).

Secondary urinary outcomes are defined by the modeled mean change from baseline in the following voiding diary measures and questionnaire scores over 24 weeks of treatment (averaged over 4, 12, and 24 weeks), as well as at 12 weeks after the end of treatment (36 weeks):Frequency of urgency-type incontinence (episodes/week)Frequency of any-type incontinence (episodes/week)Resolution of urinary incontinence (dichotomous outcome)Overactive Bladder Questionnaire Short-Form (OAB-Q SF) Symptom Bother domain score [49]Overactive Bladder Questionnaire Short-Form (OAB-Q SF) Health-Related Quality of Life domain score [49]

Secondary sleep-related outcomes are defined by the modeled mean change from baseline in scores in the following questionnaire measures over 24 weeks of treatment (averaged over 4, 12, and 24 weeks), as well as at 12 weeks after the end of treatment (36 weeks):Pittsburgh Sleep Quality Index (PSQI) global sleep quality score [50, 51]Epworth Sleepiness Scale (ESS) score [52]

Secondary physical function and balance outcomes will be defined by the modeled mean change from baseline in the following questionnaire and physical performance assessments over 24 weeks of treatment (averaged over 4, 12, and 24 weeks), as well as at 12 weeks after the end of treatment (36 weeks):PROMIS 10B Adult Physical Function Scale [53]Activities Balance Confidence Scale (ABC-S) [54, 55]Short Physical Performance Battery (SPPB) [56, 57]One-legged standing balance time [58, 59]Thirty-second chair stand test [60]

Secondary psychological function outcomes will be defined by the modeled mean change from baseline in scores in the following questionnaire measures over 24 weeks of treatment (averaged over 4, 12, and 24 weeks), as well as at 12 weeks after the end of treatment (36 weeks):Geriatric Depression Scale-15 (GDS-15) [61]Generalized Anxiety Depression-7 (GAD-7) [14] scale

Secondary bowel function outcomes will be defined by the modeled mean change from baseline in scores in the following questionnaire measures over 24 weeks of treatment (averaged over 4, 12, and 24 weeks), as well as at 12 weeks after the end of treatment (36 weeks):PROMIS Gastrointestinal Symptoms-Constipation scale [62, 63]PROMIS Bowel Incontinence scale [62, 63]

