### Sample size {14}

A sample size of 270 participants, randomized in equal proportions to the three arms, has been chosen to provide > 80% power in 2-sided tests with an experiment-wise type 1 error rate of 5%, corrected for two comparisons (anticholinergic therapy to beta-3-adrenergic agonist therapy; anticholinergic therapy to placebo) [48] to detect an average treatment effect of 0.25 standard deviation’s difference in the composite cognitive function outcome over 6 months, assuming an intraclass correlation of 0.75 among repeated cognitive outcomes, and cumulative loss to follow-up level of 15% by 6 months of treatment.

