### Data collection and management

#### Plans for assessment and collection of outcomes {18a}

Cognitive function outcomes will be assessed using a battery of neuropsychological tests (see the “Outcomes {12}” section) administered by clinical research coordinators who have completed dedicated training and certification by a neuropsychiatry or neuropsychologist investigator, who will also oversee the quality of these assessments. Whenever possible, repeated cognitive measures in the same participant will be administered by the same evaluator and use the same mode of administration (in person versus by video visit) across all study time points. Additionally, a sample of session recordings will be observed by the neuropsychologist co-investigator to ensure standardized administration across coordinators.

Frequency and type of incontinence will be assessed using a standardized, 7-day voiding diary. At baseline and outcome follow-up visits, participants will receive a blank diary and instructions on using it to record each time they leak urine as well as indicate whether the leakage is associated with a sudden or strong urge to urinate. Diary data will be abstracted by blinded analysts who have undergone study-specific training and supervised practice in reviewing and abstracting diary data to calculate the frequency of incontinence associated with urgency.

Structured self-report questionnaires will be used to assess other urinary, sleep-related, perceived physical function, psychological, and bowel function outcomes (see the “Outcomes {12}” section). Participants may complete the questionnaires electronically or alternately complete them on paper and then return them to blinded study coordinators for electronic data entry.

Physical performance and balance testing will be performed by clinical research coordinators who have completed study-specific training in these measures. Testing will be performed in person or through video-based visits, following procedures outlined in the study manual of operations, but the same mode of assessment will be preferentially used at baseline and follow-up assessments.

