## Statistical methods

### Statistical methods for primary and secondary outcomes {20a}

To examine the primary outcome, medication effects on cognitive function will be estimated using a linear mixed model (LMM) for repeated changes from the baseline of the composite cognitive function outcome, averaged at 4, 12, and 24 weeks, adjusted for baseline value. In addition to a fixed effect for study location, the LMM will include terms for time (as a categorical variable) and time-by-treatment interactions. Treatment effects will be captured by the time-by-treatment interactions and their 95% confidence intervals, focusing on the comparisons of the anticholinergic arm with each of the two other arms.

The primary hypothesis will be tested using the average of the time-by-treatment interactions at 4, 12, and 24 weeks. Persistence of treatment effects will be evaluated by examining the time-by-treatment interaction at 36 weeks, and second by contrasting the 36-week interaction with the average of the 4-, 12-, and 24-week interactions, which will capture attenuation of the on-treatment effect after an additional 12 weeks. In models involving the average of the effects at 4, 12, and 24 weeks, we will check for heterogeneity and trend across those visits. If evidence of heterogeneity is detected, we will consider examining time-by-treatment interactions at each time point (4, 12, and 24 weeks) separately.

The primary analyses will be by intention to treat among participants with at least one post-baseline follow-up assessment, according to treatment group assignment, and without regard to adherence, avoiding selection bias from informative discontinuation of treatment. However, secondary per-protocol analyses omitting those outcomes will also be performed, since the inclusion of post-discontinuation outcomes may attenuate treatment effect estimates if treatment effects are primarily acute.

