### Methods in analysis to handle protocol non-adherence and any statistical methods to handle missing data {20c}

Primary analyses will be by intention to treat among participants with at least one post-baseline follow-up assessment, according to treatment group assignment, and without regard to adherence, avoiding selection bias from informative discontinuation of treatment. However, secondary, per-protocol analyses omitting those outcomes will also be performed. If rates of participant dropout or missing data differ between the groups, multiple imputation of missing outcomes may be performed under plausible informative missingness assumptions.

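### The primary composite averages whichever tests were completed at each visit, so its change from baseline can reflect a change of test set; if tests are lost through poor performance mainly in the anticholinergic arm, harm is understated.

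*Protocol article*

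**What the plan says.** In the protocol article, Outcomes {12}, each test score is centred on the baseline mean of all randomized participants, and "this difference will be divided by the standard deviation of test scores from the baseline trial population". The composite at a visit is then the mean Z "score from all available tests completed by each participant at each visit will be calculated to provide a composite" score for that visit. The primary outcome is the modeled mean change from baseline in that composite Z "score at 4, 12, and 24 weeks, averaged over these time points". The individual scores, named as secondary outcomes, are "AVLT total learning, AVLT delayed free recall, OTMT part A, OTMT part B, Digit Span Test backward component, and DSST". The article does not say whether the composite averages these six scores or the four tests.

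The mixed model in Statistical methods {20a} takes change from baseline, "averaged at 4, 12, and 24 weeks, adjusted for baseline value". On missing data, section {20c} says: "If rates of participant dropout or missing data differ between the groups, multiple imputation of missing outcomes may be performed". The sample size section plans "to detect an average treatment effect of 0.25 standard deviation’s difference in the composite cognitive function outcome over 6 months".

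**The concern.** A participant's Z scores differ from test to test. If the set of tests averaged at week 4, 12 or 24 is not the set averaged at baseline, the difference between the two averages contains a term that has nothing to do with change in cognition. If the absent test is one of her weaker ones, that term is positive.

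The trial is looking for cognitive harm from anticholinergic therapy, and difficulty finishing a test could itself be a sign of harm. Were such losses commoner in the anticholinergic arm, the averaging rule would push the primary contrast toward no difference.

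Two other provisions might be expected to repair this, and neither does. Adjusting for the baseline composite does not restore a common test set. The imputation clause concerns missing outcomes, and under the available-test rule a participant with one test absent still has a composite.

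**Working it through.** **The plan's own figure.** Inputs from Sample size {14}: 90 per arm, effect 0.25 SD, intraclass correlation 0.75, two-sided 5% over two comparisons (0.025 each), 15% loss by 6 months.
- Variance of the mean of three follow-ups adjusted for baseline: (1 + 2 × 0.75)/3 − 0.75² = 0.8333 − 0.5625 = 0.2708.
- No loss: standard error √(2 × 0.2708/90) = 0.0776, power 83.7%.
- Cumulative loss of 5%, 10% and 15% at the three visits: standard error 0.0808, power 80.4%.

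The stated power above 80% therefore reproduces with staged loss. The issue here is bias in the estimate, not the planned power.

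**One participant.** Let m be the mean Z of the k − 1 tests that remain and z the Z of the test missing at follow-up, with nothing else changed.
- Baseline composite: ((k − 1)m + z)/k. Follow-up composite: m.
- Artefactual change: m − ((k − 1)m + z)/k = (m − z)/k.
- k = 6, m = 0, z = −1.5: +0.25. With k = 4: +0.375.
- k = 6, and the remaining five truly fall by 0.1: −0.10 + 0.25 = +0.15, so a decline reads as a gain.
- k = 6, z = +1.5: −0.25. A missing strong test moves the composite the other way.
- If the test is missing at only one of the three on-treatment visits, her average moves by 0.25/3 = 0.083.

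**Arm level.** The documents give no rate or mechanism of non-completion, so these are assumptions: k = 6, inter-test correlation 0.3-0.5, test-retest correlation 0.75, true difference 0.25 Z equal on all tests, 10-20% of participants not completing one test because they score low on it. I simulated one follow-up visit and regressed change on arm and baseline composite. The same shift must recur at all three visits to move the averaged outcome fully.

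| Who loses which test | Contrast, rule as written | Contrast, matched tests |
|---|---|---|
| Harmed arm only, one fixed test | 0.21-0.23 | about 0.24 |
| Harmed arm only, each woman's own lowest test | 0.19-0.22 | 0.23-0.24 |
| Both arms by one common threshold, own lowest test | 0.23-0.24 | 0.24-0.25 |
| Missing at random, harmed arm only | 0.25 | 0.25 |

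Against the true 0.25, informative loss costs about 0.01-0.06 Z. Matching recovers somewhat more than half of that. For example, at 20% and correlation 0.3 with only the harmed arm affected, 0.189 becomes 0.230: (0.230 − 0.189)/(0.25 − 0.189) = 0.67.

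**Units.** The planned 0.25 is in SDs of the composite. An average of k Z scores with correlation r has SD √((1 + (k − 1)r)/k), which is 0.65-0.76 for k = 6 and r = 0.3-0.5. So 0.25 SD is about 0.16-0.19 Z, and the simulated 0.25 Z is somewhat larger than the planned effect.

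**The case against.** The strongest reply is that informative, arm-differential non-completion is assumed. Nothing in the article says that a test done badly or left unfinished is recorded as missing and not as a low score. The design also makes lost tests less likely:
- The exclusions cover diagnosed dementia, a MoCA of 17 or lower, inability to complete testing in English, and conditions that prevent study procedures.
- The tests were chosen partly for feasibility.
- Testers are trained and certified, and the data system queries missing values.
- Section {18a} adds: "Whenever possible, repeated cognitive measures in the same participant will be administered by the same evaluator and use the same mode of administration". That removes one cause of changing test sets.

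All of this stands, and it limits the likely size.

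Three stronger readings are tempting, and the documents do not support them.
- A reader might infer that failing a hard test generally registers as improvement. Z-scoring removes a test's general difficulty. Only a test weak relative to the participant's own others gives a gain, and only if all Z scores run so that higher is better, which the article does not state.
- A reader might set the +0.25 beside the planned 0.25 SD and conclude that the whole effect could vanish. The first is one constructed participant's change; the second is a difference between arm means.
- A reader might say that the rule reverses the signal in those most affected. In simulations with 5-20% non-completion (k = 6), 30-42% of affected participants read as improved, against 12-14% with full data, so most still do not.

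It can also be said that minimum test counts and reason codes belong in an analysis plan or manual that is not shown. That is fair, and their absence is not the point. The averaging rule is stated in the article, for the primary outcome. Separate analyses of each test may reveal unequal loss, and the imputation clause could then be invoked for those scores, but it is discretionary and leaves the composite rule as it is.

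**Conclusion.** The point holds as a weakness in a stated rule with a cheap and better alternative. It is not evidence that the trial will miss harm. The available-test average lets change from baseline compare different test sets, and neither baseline adjustment nor the optional imputation corrects that.

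Under the assumptions in the table, a true difference of 0.25 Z is attenuated by about 0.01-0.06 Z, that is 4-24% of it (0.01/0.25 to 0.06/0.25). The upper end needs losses confined to the harmed arm, in 20% of women, on each woman's weakest test, at every on-treatment visit. Sharing one threshold across arms brings the loss to about 0.01-0.02 Z, and random missingness causes almost none. With four components instead of six, each lost test weighs more.

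**What to change.** Define each visit's composite change as the mean change over the tests present at both baseline and that visit, and keep the full baseline composite as the model covariate so that all visits share one adjustment variable. A minimum number of completed tests is no substitute: in the worked example five of six scores are present, which a minimum such as four of six would accept.

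Matching removes only part of the bias, because the lost test may be the one that declined. So:
- Record on the test form why a test was not done, separating inability from technical or scheduling reasons.
- Add a sensitivity analysis that imputes at test-score level before averaging.
- Add another that gives a prespecified floor score to tests not completed for cognitive reasons. This is a strong assumption and is better kept out of the primary analysis.
- State that every Z score is oriented so that higher is better, and which scores enter the composite.

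The cost is a few lines of analysis text, slightly more programming and one extra field on the form. It should be settled before study-wide unblinding.

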### Participant timeline {13}

Participants complete the screening measures before randomization at a baseline visit that must take place within 2 months (60 days) of screening. Initiation of interventions begins immediately after randomization, after which participants are scheduled for follow-up at 2 weeks for consideration of study medication dose titration. Follow-up visits to collect data for the trial’s primary and secondary on-treatment outcomes take place at 4 weeks, 12 weeks, and 24 weeks. An additional 36-week visit is scheduled to collect data on the potential persistence of treatment effects 12 weeks after participants have discontinued study treatment (Fig. 1).

**Fig. 1 Fig1:**
[figure not shown]
Study design

### Sample size {14}

A sample size of 270 participants, randomized in equal proportions to the three arms, has been chosen to provide > 80% power in 2-sided tests with an experiment-wise type 1 error rate of 5%, corrected for two comparisons (anticholinergic therapy to beta-3-adrenergic agonist therapy; anticholinergic therapy to placebo) [48] to detect an average treatment effect of 0.25 standard deviation’s difference in the composite cognitive function outcome over 6 months, assuming an intraclass correlation of 0.75 among repeated cognitive outcomes, and cumulative loss to follow-up level of 15% by 6 months of treatment.

### Recruitment {15}

The TRIUMPH trial team is using a multi-pronged recruitment approach to recruit older ambulatory incontinent women residing in multiple communities in northern California. Study candidates are identified through community-based recruitment strategies, such as the mailing of recruitment letters to households in northern California using commercial mailing services; posting of recruitment fliers in local senior centers, community organizations, or businesses; recruitment advertisements placed in regional newspapers; and/or online social media-based recruitment. Recruitment may also include mailings to current and past female patients aged 60 years or older who have received healthcare services from UCSF Health and Stanford Medical Center as the healthcare delivery systems associated with the study institutions, as well as recruitment from a database of past participants from other UCSF or Stanford-based studies of urinary symptoms or cognitive decline.

### Assignment of interventions: allocation

#### Sequence generation {16a}

Eligible participants are randomized in a fixed 1:1:1 ratio to each of the study arms, with stratification by study site (UCSF versus Stanford University), using randomly permuted blocks of sizes of 4 and 6. The randomization scheme has been generated by computer by a statistician independently contracted through the UCSF Clinical and Translational Science Institute.

#### Concealment mechanism {16b}

An independent statistician has been contracted to prepare the allocation sequence, provide the sequence to the research pharmacy responsible for dispensing study medication, and upload the sequence into the electronic study data system, where it is concealed from the trial investigators, coordinators, and statistical programmers.

#### Implementation {16c}

At baseline, after screening data have been reviewed and eligibility has been confirmed, a blinded coordinator enters the date into the electronic data system to retrieve the randomization number, which enforces temporally sequential randomization assignments. The coordinator submits the randomization number to the contracting research pharmacy, who identifies and dispenses the study medication lot associated with the randomization number.

